### Cost-effectiveness

All patients will be asked to complete the following questionnaires at T1, T2 and T3 together with the measurements for clinical effectiveness (see Fig. 1). These questionnaires will be sent to the patient by mail or by email (see Table 1).

The following measurements will be completed:
*Five-Dimensional EuroQol (EQ-5D-5L)*

The EQ-5D-5L is explained above.
2.*Medical Consumption Questionnaire (MCQ)*

Health care costs will be measured by a slightly adapted version of the MCQ [31]. The MCQ consists of 30 questions focusing on the last period, i.e. 6 weeks, 6 weeks and 9 months. The number of visits to health care professionals are registered. The type, duration and hours per day of home care is examined as well. Besides, the number of ambulance transferrals, hospital admissions and any other admission are recorded. The MCQ will be completed by the patient at home.
3.*Productivity Cost Questionnaire (PCQ)*

Family costs and costs outside the health care sector will be recorded by the PCQ [32]. The questionnaire encompasses 18 questions of which six are about demographic characteristics. The remaining questions consist of three modules, namely loss of productivity in paid work due to 1) absenteeism (absence of work) or 2) presenteeism (health related diminished-productivity at work) and 3) productivity loss in unpaid work. The questions specifically focus on productivity in the last 4 weeks. The PCQ will be completed by the patient at home.

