### Intervention group

In the intervention group, patients receive an intervention that consists of a face-to-face consultation of approximately 60 min at the outpatient clinics of the neurology department in addition to usual care. This intervention will take place at approximately 6 weeks after the stroke with a maximum range of 2 weeks earlier or later. A maximum of one follow-up session after the initial consultation may be proposed by the nurse if needed, but this is not obligatory. When more follow-up sessions seem to be needed, referral for specialized (rehabilitation) care will be advised; which specialized care that will be, depends on the problems experienced and the local health care situation. The consultation will be executed by a specialized nurse, nurse practitioner or physician assistant who is experienced in and currently performs outpatient care for patients with stroke at the participating center; hereinafter referred to as ‘nurse’. If a nurse is not available in an eligible center, one of the researchers (JS) will perform the intervention.

The intervention includes:
a structured screening for cognitive and emotional problems using sensitive instruments: the Checklist for Cognitive and Emotional Consequences following stroke (CLCE-24), the Montreal Cognitive Assessment (MoCA) (if the MoCA has been performed at an earlier moment after stroke and the score was ≥26, the MoCA does not need to be repeated) and the Hospital Anxiety and Depression Scale (HADS);a structured screening for restrictions in participation by the USER-Participation-R;self-management support consisting of the following elements: a) providing timely and individualized oral and written information about stroke and its possible cognitive and emotional sequelae, b) measuring self-efficacy by the Dutch General Self-Efficacy Scale (GSES) and providing patient-tailored guidance, c) achieving shared-decision making and d) providing contact details for possible additional questions or problems;a decision tool for referral to rehabilitation services based on the results of the screening instruments. Generally, if patients experience one or more participation restriction(s), as measured by the USER-Participation-R, due to the recent ischemic stroke, referral to rehabilitation services will be indicated, but is not obliged. Besides, a close cooperation with the physiatrist will be advised, in order to decide upon optimal follow-up care.

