### Primary outcome measure

#### Clinical effectiveness

The primary outcome measure will be the level of participation measured with the USER-Participation-R [22]. The USER-Participation-R will be completed at 6 weeks (T1), 3 months (T2) and 12 months (T3) after stroke.

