#### Cost-effectiveness

Quality of life will be measured with the Five-Dimensional EuroQol (EQ-5D-5L). Costs will be assessed with the Medical Consumption Questionnaire (MCQ) and the Productivity Cost Questionnaire (PCQ) [29–31]. The following cost categories will be distinguished: intervention costs, health care costs, patient and family costs and costs outside the health care sector (productivity). Data for the economic evaluation will be collected at T1, T2 and T3.

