#### Clinical effectiveness

In the centers that are randomized to the intervention group, patients will visit the neurologic outpatient clinic for the intervention approximately 6 weeks after their stroke. Patients will be asked to complete the questionnaires sent by mail and bring them along to the consultation (see Table 1). The results from the USER-Participation-R, CLCE-24, HADS and GSES will be used by the nurse for additional questioning and individualized counselling; however, the results of the completed questionnaires will not be changed. Besides, the MoCA will be completed by the nurse during the consultation (T1). The other questionnaires will be collected during the consultation, but will only be used for research purposes. Follow-up moments at T2 and T3 include questionnaires that will be sent by mail or email (see Table 1).

**Table 1 Tab1:** Overview of baseline and follow-up measurements

	measurements	baseline (T0)	6 weeks (T1)	3 months (T2)	12 months (T3)

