**Secondary outcomes**					
cognitive and emotional complaints	CLCE-24^a^		x^a^	x	x
symptoms of depression and anxiety	HADS^a^		x^a^	x	x
physical disability	mRS	x		x	x
self-efficacy	GSES^a^		x^a^	x	x
global health	PROMIS Global-10		x	x	x
patient satisfaction with stroke-care	customized version of SASC-19			x	
quality of life	EQ-5D-5L		x	x	x
cost questionnaires	MCQ PCQ		x	x	x

*NIHSS* National Institute of Health Stroke Score; *mRS* Modified Rankin Scale; *USER-Participation-R*, Restriction subscale of the Utrecht Scale for Evaluation of Rehabilitation on the level of Participation; *CLCE-24* Checklist for Cognitive and Emotional Consequences following stroke; *MoCA* Montreal Cognitive Assessment; *HADS* Hospital Anxiety and Depression Scale; *GSES* Dutch adaptation of the General Self-Efficacy Scale; *PROMIS Global-10* Patient Reported Outcome Measurement Information System; *SASC-19* Satisfaction with Stroke-Care; *EQ-5D-5L* Five-Dimensional EuroQol; *MCQ*, Medical Consumption Questionnaire; *PCQ* Productivity Cost Questionnaire

^a^
*those questionnaires will be used as both a screening instrument and an outcome measurement*

In the centers that are randomized to usual care, patients will be asked to complete the questionnaires at T1, T2 and T3 (Fig. 1). These questionnaires will be sent to the patient by mail or by email (see Table 1).

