### Process evaluation

A process evaluation was developed in accordance with the framework of the Medical Research Council and consists of the following parts: [33].
*Reach and Dose of the Intervention*

The reach of the intervention is defined as the number of patients actually included in the study, divided by the total number of patients that were screened for eligibility. This information will be registered in a screening log.

The dose of the intervention is defined as the number of patients actually receiving the intervention, divided by the total number of patients included in the study. This information will be registered in the electronic case report form (eCRF).
2.*Fidelity to the Intervention Protocol*

The fidelity is defined as the adherence to the original intervention protocol. The fidelity to the following components of the intervention will be registered. First, the protocol prescribes that the intervention should be performed within four to 8 weeks after the ischemic stroke. The timing of the intervention will be registered in the eCRF. Second, patient charts and eCRF will be used to register if the patient brought the completed questionnaires to their appointment. Third, in the patient charts will be registered if the nurse completed the screenings instruments during the consultation. Fourth, in the eCRF will be registered if the nurse provided individualized information and if shared decision making took place. Fifth, the nurse will register in the eCRF if the intervention could be completed within the estimated time. In addition, in a focus group interview, the nurses will be asked for experience with the application of the intervention in their daily care and the adherence to the intervention protocol for more profound understanding of possible deviations from the protocol.
3.*Contextual Factors*

Contextual factors that might affect implementation are measured by the Barriers and Facilitators Assessment Instrument (BFAI) [34]. The BFAI will be completed by the nurse after he/she delivered the intervention to ten study patients and before the focus group interview takes place. During this interview, additional information will be gathered to get a more profound understanding of the barriers and facilitators nurses reported in the BFAI during this interview for further questioning.
4.*Patient Satisfaction*

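### If the fixed MCQ recall lengths are applied literally, up to 2–3 weeks of care straight after an early consultation go unrecorded, because T1 in the intervention arm can fall anywhere in weeks 4–8

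*Protocol article*

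**What the plan says.** All places are in the Protocol article.

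- **Recall lengths** (Data collection, Cost-effectiveness, item on the Medical Consumption Questionnaire): "The MCQ consists of 30 questions focusing on the last period, i.e. 6 weeks, 6 weeks and 9 months".
- **Visit dates** (Primary outcome measure): "The USER-Participation-R will be completed at 6 weeks (T1), 3 months (T2) and 12 months (T3) after stroke". The cost forms go out at the same points: "All patients will be asked to complete the following questionnaires at T1, T2 and T3 together with the measurements for clinical effectiveness".
- **Timing of the consultation** (Intervention group): "This intervention will take place at approximately 6 weeks after the stroke with a maximum range of 2 weeks earlier or later". The fidelity item under Process evaluation gives the same window: "the intervention should be performed within four to 8 weeks after the ischemic stroke".
- **T1 form, intervention arm** (Data collection, Clinical effectiveness): "Patients will be asked to complete the questionnaires sent by mail and bring them along to the consultation".
- **T1 form, control arm** (text below Table 1): "In the centers that are randomized to usual care, patients will be asked to complete the questionnaires at T1, T2 and T3". These forms come by mail or email. No visit and no completion window is attached to them.

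**The concern.** The article fixes how far back each MCQ looks, but one of the dates it looks back from can move. By design, T1 in the intervention arm may lie up to 2 weeks either side of week 6. A recall of constant length counted back from T2 then no longer meets T1: it stops short of an early T1 and runs past a late one.

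This matters for two reasons. The weeks that an early consultation leaves uncovered come straight after it, when the optional follow-up session and any referral can start to generate cost. And the movement of T1 with the consultation exists in one arm only, so there is no reason to expect the same pattern of gaps and overlaps in both arms. Cost-effectiveness is one of the trial's three stated objectives, and use of care that no form asked about cannot be recovered later from the MCQ.

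**Working it through.** **Inputs.** Recall of 6 weeks at T1, 6 weeks at T2 and 9 months (39 weeks) at T3. Nominal visits at week 6, 3 months and 12 months (week 52). Consultation, and so T1 in the intervention arm, at week t with t from 4 to 8.

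**Assumptions.** T2 is on time. Three months is read as week 12 or week 13, since the article does not say which. The T1 form is dated at the consultation. Recall is taken literally.

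**1. The plan's own schedule.** 6 + 6 + 39 = 51 of 52 weeks. If T2 is at week 13, the missing week lies between T1 and T2 (13 − 6 − 6 = 1). If T2 is at week 12, it lies between T2 and T3 (52 − 39 − 12 = 1). With every visit on its nominal date, the lengths fit to about 1 week.

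**2. Letting T1 move.**

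- Start of T1 recall = t − 6. A negative value reaches back before the stroke; a positive value leaves the first weeks after stroke uncovered.
- Start of T2 recall = T2 − 6, which is week 6 or week 7.
- Gap = (T2 − 6) − t. Positive means unrecorded, negative means counted twice.

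| T1 (week t) | T1 recall starts | Gap, T2 = week 12 | Gap, T2 = week 13 |
|---|---|---|---|
| 4 | −2 | 2 | 3 |
| 5 | −1 | 1 | 2 |
| 6 | 0 | 0 | 1 |
| 7 | 1 | −1 | 0 |
| 8 | 2 | −2 | −1 |

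**3. Share of the T1–T2 interval lost at t = 4.** 2/(12 − 4) = 25%, or 3/(13 − 4) = 33%.

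**4. Where the overlap lies at t = 8.** T2 recall starts at week 6 or 7 and T1 recall ends at week 8. The doubly counted time is weeks 6–8 or 7–8, all of it before the consultation. The T1 recall starts at week 2, so weeks 0–2 are outside it.

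**5. Average rather than extreme.** Suppose t is uniform over weeks 4–8; this is an assumption, as the article gives no distribution. The mean unrecorded time after the consultation is then (2²/2)/4 = 0.5 weeks for T2 at week 12 and (3²/2)/4 = 1.1 weeks for T2 at week 13.

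**6. With recall anchored to dates.** If T2 recall starts at the actual T1 date, gap = t − t = 0 for every t. If T1 recall starts at the stroke, no early weeks are lost and none before the stroke are included.

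**The case against.** The strongest reply is that the wording refers to the last period and then gives the nominal spacings as a gloss. On that reading the form may already ask about the time since the previous questionnaire. The form is not shown, so this cannot be excluded. It stands as a reason to rank the point low, but it does not remove it: the stated lengths would then be wrong for anyone not seen at week 6, and the text would still need correcting.

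Two further replies stand. The 2–3 weeks are the extreme of a window centred on week 6. And the consultation itself is not exposed to the gap, because intervention costs are a separate category and the timing of the intervention is registered in the eCRF.

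A reader might also infer stronger conclusions, which the article does not support:

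- *Care after the consultation is counted twice.* It is not. With T2 on time, the overlap lies before the consultation (step 4).
- *The intervention is made to look cheaper.* The direction is not shown. Lost weeks lower recorded cost in the intervention arm, but early T1 forms that reach back before the stroke, and late forms with overlap, raise it. Nor need the index stay be lost when T1 is late: Table 1 records its duration at T0, so it can be costed without patient recall.
- *Costs from before the consultation enter the ICER, while utilities start only at T1.* The economic data do begin at T1 ("Data for the economic evaluation will be collected at T1, T2 and T3"), and the first MCQ looks back to about the stroke. But the statistical section on cost-effectiveness gives no interval for costs or QALYs, and an article may leave that to the economic plan. T1 costs could serve as a baseline covariate. If weeks 0–6 were included, the consultation could not have changed costs or QALYs in that time, so both increments would be zero in expectation.

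**Conclusion.** The point holds as a minor one. The recall lengths suit the nominal schedule to within about 1 week; the defect comes from pairing fixed lengths with a T1 that may move over 4 weeks in the intervention arm only. Read literally and with T2 on time, 2–3 weeks of care straight after a week-4 consultation are unrecorded (25–33% of the interval to T2). At week 8, weeks 0–2 fall outside the T1 recall and 1–2 pre-consultation weeks are counted twice. A week-6 consultation leaves a gap of 0–1 week.

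These figures rest on a literal fixed recall, on T2 being on time, and on 3 months meaning week 12 or 13. The article gives no unit costs, no volumes of care and no distribution of T1 dates, so the effect on incremental cost can be given neither a sign nor an amount.

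**What to change.** Anchor each MCQ to dates rather than to a fixed length, and print the date on the form:

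- T1: since your stroke on [date].
- T2 and T3: since your previous questionnaire on [date].

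In the article's MCQ description, say that 6 weeks, 6 weeks and 9 months are the nominal lengths of these periods. This removes gap and overlap for every T1 in weeks 4–8, in both arms.

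The cost is small: a change of wording on a form that the trial already modifies, and the merging of the stroke date and the date of the previous questionnaire into each mailing. The downside is that recall length varies slightly between patients. If the form already asks in this way, correcting the sentence in the article is enough.

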### Process evaluation

A process evaluation was developed in accordance with the framework of the Medical Research Council and consists of the following parts: [33].
*Reach and Dose of the Intervention*

The reach of the intervention is defined as the number of patients actually included in the study, divided by the total number of patients that were screened for eligibility. This information will be registered in a screening log.

The dose of the intervention is defined as the number of patients actually receiving the intervention, divided by the total number of patients included in the study. This information will be registered in the electronic case report form (eCRF).
2.*Fidelity to the Intervention Protocol*

The fidelity is defined as the adherence to the original intervention protocol. The fidelity to the following components of the intervention will be registered. First, the protocol prescribes that the intervention should be performed within four to 8 weeks after the ischemic stroke. The timing of the intervention will be registered in the eCRF. Second, patient charts and eCRF will be used to register if the patient brought the completed questionnaires to their appointment. Third, in the patient charts will be registered if the nurse completed the screenings instruments during the consultation. Fourth, in the eCRF will be registered if the nurse provided individualized information and if shared decision making took place. Fifth, the nurse will register in the eCRF if the intervention could be completed within the estimated time. In addition, in a focus group interview, the nurses will be asked for experience with the application of the intervention in their daily care and the adherence to the intervention protocol for more profound understanding of possible deviations from the protocol.
3.*Contextual Factors*

Contextual factors that might affect implementation are measured by the Barriers and Facilitators Assessment Instrument (BFAI) [34]. The BFAI will be completed by the nurse after he/she delivered the intervention to ten study patients and before the focus group interview takes place. During this interview, additional information will be gathered to get a more profound understanding of the barriers and facilitators nurses reported in the BFAI during this interview for further questioning.
4.*Patient Satisfaction*

As the intervention focusses on improving care for patients with cognitive or emotional problems after ischemic stroke, participant responsiveness will be measured in terms of patient satisfaction. Patient satisfaction will be assessed by the Satisfaction with Stroke Care (SASC-19) questionnaire in the intervention group and the control group at T2 [35]. Since the first eight items of the original SASC concern the hospital admission, these items will not be administered. Two items will be added to the questionnaire, concerning shared-decision making and individualized information provision. The customized SASC-19 will be completed by the patient at home.

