**Methods / design:**

A multicenter, patient-blinded, cluster randomized controlled trial will be performed. Centers will be randomized (1:1) to the intervention group or the usual care group. Patients (> 18 years old) with a neurological confirmed diagnosis of ischemic stroke who can be discharged home without follow-up treatment at an outpatient rehabilitation clinic will be included. In the intervention group, patients will receive a short, individualized, semi-structured consultation by specialized nurses in addition to usual care. This consultation includes 1) screening for cognitive and emotional problems, 2) screening for restrictions in participation, 3) promotion of self-management strategies and 4) a decision tool for referral to rehabilitation services. The intervention will be performed approximately 6 weeks after the stroke at the neurology outpatient clinics and will take approximately 60 min. The control group will receive care as usual. Both groups will be followed-up at 6 weeks, 3 months and 12 months after stroke. The primary outcome will be the level of participation measured with the Restriction subscale of the Utrecht Scale for Evaluation of Rehabilitation on the level of Participation (USER-Participation-R) at 12 months. A cost-effectiveness analysis and process evaluation will be performed alongside.

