### Trial center eligibility and allocation

University and non-university hospitals in the Netherlands will be invited to participate in this study. All centers that intend to participate will be examined for their current stroke care by an online questionnaire and by interviews. Centers will be excluded from the study if one of the following criteria is met:
the current stroke care includes a screening for cognitive and emotional problems using validated screening instruments in the majority of stroke patients, within 3 months after stroke;the current stroke care includes long term follow-up (6 months or longer) with repeated cognitive and emotional assessments, with or without the use of validated screening instruments, in the majority of stroke patients.

After selection, the eligible centers will be randomized by an independent statistician in blocks of two in a 1:1 ratio to the intervention group or the usual care group using the web-based system Randomizer [20].

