### Sample size

Since no USER-Participation-R data are available concerning the participation levels of our target group, we based our sample size calculation on Cohen’s effect size as benchmark for assessing the relative magnitude of differences in participation level between the treatment arms. Although a Cohen’s effect size of 0.35 can be defined as between small and medium, such a difference in mean participation scores may be clinically important. Therefore, it was considered necessary to detect this difference in participation level between both treatment arms. A sample size of six clusters per treatment group (12 clusters in total) with 36 individuals per cluster (216 patients per treatment group; 432 patients in total) achieves 81% power to detect an effect size of 0.35 when the intracluster correlation is 0.01 using a two-sided t-test based on the number of clusters, with a significance level of 0.05 [21]. Anticipating on a 15% attrition rate in each center, we will include (36 / 0.85 =) 43 patients per center, resulting in 258 patients per treatment group and 516 patients in total.

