### Control group

In the control group, patients will receive care as usual according to the current protocol of the participating hospital. The local protocol probably varies among the various hospitals.

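### Dose of the intervention is divided by all study patients, so as defined it measures delivery multiplied by the intervention arm's share of recruitment

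*Protocol article*

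**What the plan says.** In the Process evaluation section under data collection, the item on reach and dose gives both quantities an explicit numerator and denominator. Dose is "defined as the number of patients actually receiving the intervention, divided by the total number of patients included in the study". The sentence just before it uses the same study-wide count as a numerator: "The reach of the intervention is defined as the number of patients actually included in the study", set against all patients screened for eligibility.

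The design sections fix who can receive the intervention:

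- Abstract, Methods / design: "Centers will be randomized (1:1) to the intervention group or the usual care group". Trial center eligibility and allocation adds that this is done "in blocks of two in a 1:1 ratio to the intervention group or the usual care group".
- Intervention group: "In the intervention group, patients receive an intervention that consists of a face-to-face consultation of approximately 60 min".
- Control group: "In the control group, patients will receive care as usual according to the current protocol of the participating hospital".
- Sample size: "43 patients per center, resulting in 258 patients per treatment group and 516 patients in total".

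The later Process evaluation paragraph under statistical analysis says only that reach and dose will be described. It gives no other denominator.

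**The concern.** A measure of delivery should equal 100% when every patient who was meant to get the consultation got it. This one does not, because its denominator includes a whole arm that is not offered the consultation. The reported percentage then mixes two things: how well the intervention centers delivered, and how the recruited patients happened to split between arms.

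Implementation is one of the trial's three stated objectives, and the effectiveness analysis follows intention to treat, so missed consultations dilute any effect. Readers will want to know what share of intervention patients had the consultation. Dose is the listed measure that states this as a proportion, and as written it would understate delivery by about half at the planned recruitment.

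This is not a detail left to a fuller document. The article states the rule, and the rule gives the wrong number for its purpose.

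**Working it through.** **1. The plan's own figures.** Sample size section: 36 patients per cluster, six clusters per group, 15% attrition.

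- 36 / 0.85 = 42.35, rounded up to 43 per center
- 43 × 6 = 258 per group
- 43 × 12 = 516 in total

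These match the article. The stated power is also reproduced. The design effect is 1 + (36 − 1) × 0.01 = 1.35, the noncentrality is 0.35 / √(2 × 1.35 / 216) = 3.130, and a two-sided t-test at 0.05 with 12 − 2 = 10 degrees of freedom gives 80.5%, against the stated 81%. Dose plays no part in this calculation. The article states no figure for dose itself.

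**2. What the definition computes.** Let R be the number of patients who receive the consultation, all in the intervention arm, and let N_I and N_C be the patients included in the intervention and usual-care arms.

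- Dose as written = R / (N_I + N_C) = (R / N_I) × N_I / (N_I + N_C)

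The first factor is delivery. The second is the intervention arm's share of included patients.

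**3. At the planned recruitment.** The share is 258 / 516 = 0.50. It would also be 0.50 among the 432 patients the power calculation needs: 216 / 432.

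| Delivery in the intervention arm | Dose as written | Dose with intervention-center denominator |
|---|---|---|
| 100% | 1.00 × 0.50 = 50% | 100% |
| 95% | 0.95 × 0.50 = 47.5% | 95% |
| 90% | 0.90 × 0.50 = 45% | 90% |
| 80% | 0.80 × 0.50 = 40% | 80% |
| 70% | 0.70 × 0.50 = 35% | 70% |

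**4. If recruitment is uneven.** The arms are balanced by center, so patient numbers can differ. As an illustration only (the plan is for 12 centers), take nine centers of equal size:

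- Five intervention centers: share 5 / 9 = 55.6%. Full delivery reads 55.6%, and 90% delivery reads 0.90 × 0.556 = 50%.
- Four intervention centers: share 4 / 9 = 44.4%. Full delivery reads 44.4%, and 90% delivery reads 0.90 × 0.444 = 40%.

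The same 90% delivery is thus reported as 40% or 50%, depending only on the split between arms.

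**The case against.** The best counter-argument is that the authors meant patients at intervention centers. The sentence sits under a heading about the intervention. The fidelity items and the nurse questionnaire on barriers and facilitators that follow it can apply only at those centers. Where the process evaluation intends both arms, as for patient satisfaction, it says so. This reading is possible, and the article does not prove that the team will report full delivery as 50%. But the text does not say it. The neighboring reach definition counts included patients with no restriction to an arm, and elsewhere the article names the intervention group when it means only that group, as for the nurse-administered cognitive instruments. The plain reading is study-wide.

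A second argument is that the consequence is small and recoverable. This stands. Dose is only described, it enters no test or threshold, and receipt is recorded for each patient, so the right percentage can be calculated later. That limits the weight of the point but does not make the definition correct.

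Three stronger readings are tempting and are not supported:

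- *Dose can never exceed 50%.* The ceiling is the intervention arm's share of included patients. It equals 50% only if recruitment is equal, as planned.
- *Dose decides whether a null result means failed intervention or failed delivery.* The process evaluation also covers fidelity (timing, questionnaires brought, screening completed, information and shared decisions, duration), a nurse focus group, contextual factors and satisfaction. Poor delivery would show in several of these.
- *Reach is wrong too.* Included over screened is openly defined and usable. Preferring eligible patients as the denominator, or a split by arm, is a reporting choice; the article shows no error there.

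**Conclusion.** The dose definition is wrong as written. At the planned 258 of 516 it halves the delivery rate, so that complete delivery reads 50% and 90% delivery reads 45%. With unequal recruitment it also shifts for reasons unrelated to delivery.

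This rests on two assumptions: that usual-care patients do not receive the study consultation, as the design states, and that the denominator means what it literally says. The exact factor of one half also requires equal recruitment by arm.

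The point is modest. It concerns one descriptive measure serving one of the three objectives. The sample size and the primary analysis are unaffected.

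**What to change.** Define dose as the number of patients who received the consultation divided by the number of patients included in the intervention centers, and give both counts beside the percentage. This changes one phrase. Receipt of the intervention is already to be registered in the electronic case report form, and each patient's arm follows from the center, so no new data are needed.
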